# Engaging Moms on Teen Indoor Tanning Through Social Media: Protocol of a Randomized Controlled Trial

**DOI:** 10.2196/resprot.6624

**Published:** 2016-11-29

**Keywords:** skin cancer, indoor tanning, melanoma, Facebook, social media, health communication

## Abstract

**Background:**

Indoor tanning elevates the risk for melanoma, which is now the most common cancer in US women aged 25-29. Public policies restricting access to indoor tanning by minors to reduce melanoma morbidity and mortality in teens are emerging. In the United States, the most common policy restricting indoor tanning in minors involves parents providing either written or in person consent for the minor to purchase a tanning visit. The effectiveness of this policy relies on parents being properly educated about the harms of indoor tanning to their children.

**Objective:**

This randomized controlled trial will test the efficacy of a Facebook-delivered health communication intervention targeting mothers of teenage girls. The intervention will use health communication and behavioral modification strategies to reduce mothers’ permissiveness regarding their teenage daughters’ use of indoor tanning relative to an attention-control condition with the ultimate goal of reducing indoor tanning in both daughters and mothers.

**Methods:**

The study is a 12-month randomized controlled trial comparing 2 conditions: an attention control Facebook private group where content will be relevant to teen health with 25% focused on prescription drug abuse, a topic unrelated to tanning; and the intervention condition will enter participants into a Facebook private group where 25% of the teen health content will be focused on indoor tanning. A cohort of 2000 mother-teen daughter dyads will be recruited to participate in this study. Only mothers will participate in the Facebook groups. Both mothers and daughters will complete measures at baseline, end of intervention (1-year) and 6 months post-intervention. Primary outcomes include mothers’ permissiveness regarding their teenage daughters’ use of indoor tanning, teenage daughters’ perception of their mothers’ permissiveness, and indoor tanning by both mothers and daughters.

**Results:**

The first dyad was enrolled on March 31, 2016, and we anticipate completing this study by October 2019.

**Conclusions:**

This trial will deliver social media content grounded in theory and will test it in a randomized design with state-of-the-art measures. This will contribute much needed insights on how to employ social media for health behavior change and disease prevention both for indoor tanning and other health risk behaviors and inform future social media efforts by public health and health care organizations.

**ClinicalTrial:**

Clinicaltrials.gov NCT02835807; https://clinicaltrials.gov/ct2/show/NCT02835807 (Archived by WebCite at http://www.webcitation.org/6mDMICcCE).

## Introduction

### Indoor Tanning, Melanoma, and Public Policy

Indoor tanning elevates the risk for melanoma [1,2], which is now the most common cancer in women aged 25-29 [3,4]. Reducing indoor tanning by minors can prevent ultraviolet radiation exposure, a human carcinogen in the same class as arsenic and tobacco [2] and a primary risk factor for melanoma especially at young ages [5-11]. Indoor tanning before age 40 doubles the risk of melanoma; each tanning bed use per year increases risk for melanoma by 1.8% [12,13]. The increase in melanoma is especially evident in young, non-Hispanic, white women, paralleling the rise in their indoor tanning over the same period [14]. The Centers for Disease Control’s (CDC) Healthy People 2020 and Surgeon General’s Call to Action to Prevent Skin Cancer [15] have set the goal of reducing the prevalence of indoor tanning by teens. Currently, 10% to 15% of teens [16-20] (mainly girls) and 8% to 14% of caregivers [17,21-24] (mainly mothers) reported indoor tanning in the past year. Despite the substantial risk, indoor tanning remains popular among older adolescent females and mothers aged 27-45 [25].

Public policies restricting access to indoor tanning by minors to reduce melanoma morbidity and mortality in teens are emerging. Policy interventions can alter risk perceptions, preferences for risky behaviors, and barriers to change [26-28]. Currently, 29 states require parental permission for minors to indoor tan. Fewer states (n=24) have adopted indoor tanning regulations with age restrictions on access to tanning facilities, with just 13 states and 1 territory banning all minors under 18, making parental-permission regulations far more common than complete bans. Policies restricting minors’ access to indoor tanning will only reduce melanoma morbidity and mortality if the tanning industry complies with them [29,30]), states enforce them, and in the case of parental permission laws, parents withhold permission from teens who want to indoor tan. Unfortunately, research suggests that parental permission policies are not currently reducing rates of indoor tanning by minors [18] due to industry noncompliance, insufficient policy enforcement [29,30], and the fact that many parents fail to recognize the dangers of indoor tanning [22,31]. Exemplifying the latter, one study found 51% of mothers exhibited very little knowledge of the health consequences of indoor tanning [22]. Most (79%) also did not know that a “base tan” from a tanning bed is not protective and many (40%) were not aware that indoor tanning is potentially more harmful to teens than adults [31]. This lack of knowledge may be due to poor dissemination of information. The Food and Drug Administration provides some guidelines for exposure limits but it has only recently required facilities to post warnings on tanning beds [32-34].

Health communication that maximizes the effectiveness of indoor tanning policy, including both parental consent and bans, might activate mothers to protect their teen daughters from the harms. The current study fills this gap in the literature by testing a social media–delivered intervention developed to educate mothers and urge them to withhold permission for daughters to indoor tan. Mothers are an important target because their permissiveness and tanning behavior are strong predictors of daughters’ indoor tanning [18,22,31]. For instance, past-year indoor tanning rates are as high as 30% to 55% in teens whose mothers tan indoors [18,22,31]. Teen girls often report initiating indoor tanning with their mothers [35]. Further, girls whose first indoor tanning experience is with their mothers begin at an earlier age, become more habitual tanners, and are more resistant to change [35]. Recent research indicates that well-crafted communication can reduce maternal permissiveness about indoor tanning [36], but such communication has not been tested as a strategy specifically for maximizing indoor tanning policies. This trial leverages both health communication and behavioral strategies to improve the impact of public health policy. A social media campaign for mothers has the potential to reduce not only the prevalence of indoor tanning in adolescent girls but also the incidence of melanoma in young women. If effective, it could also easily and inexpensively be delivered by cancer-related public health organizations, many of which have social media feeds.

The present paper describes the design and methods of a randomized controlled trial of a Facebook-delivered health communication intervention to reduce mothers’ permissiveness regarding their teenage daughters’ use of indoor tanning, reduce their teenage daughters’ perception of their mothers’ permissiveness, and reduce indoor tanning by both mothers and daughters.

### Hypotheses

The primary hypothesis is that the intervention will significantly reduce mothers’ permissiveness regarding their daughters’ indoor tanning, their daughters’ perception of maternal permissiveness toward indoor tanning, and both mothers’ and daughters’ indoor tanning relative to the control condition. The secondary hypothesis is that a significantly greater number of mothers will support a ban on indoor tanning for minors in the intervention group compared with the control condition.

## Methods

### Pilot Data

Pilot interviews were conducted with 19 mothers of teenage daughters. Interviews included opinions of indoor tanning, indoor tanning policy, and health topic concerns as they relate to their daughters. Overall, 84% (16/19) were concerned about their daughters going indoor tanning, however 32% (6/19) would allow it. Most (16/19, 84%) would sign a petition supporting an indoor tanning ban for minors. Obesity and sexual activity were the greatest health concerns for daughters (both: 5/19, 31%), followed by drug and alcohol use (4/19, 26%), exercise (3/19, 16%), nutrition (3/19, 16%), mental health (3/19, 16%), cancer (2/19, 11%), and sleep (1/19, 5%). Most (15/19, 79%) mothers reported that they get health information from the Internet. This pilot study confirmed that many mothers would benefit from messages about the harms of allowing their daughters to indoor tan. It also helped us identify health topics of high interest to mothers.

### Study Design

The study design is a randomized controlled trial comparing 2 conditions over 1 year (Figure 1). Participants will be recruited in waves of approximately 84 and then randomized into the intervention or control condition. We continue in this way until a total of 25 waves have been enrolled, producing 25 groups in the intervention condition and 25 groups in the control condition each with approximately 42 participants. Participants will be blinded to condition and assessment points will occur at baseline, end of intervention (1-year), and 6 months postintervention.

**Figure 1 figure1:**
[figure not shown]
Study design.

### Intervention Condition

In the intervention condition, participants will enter a private Facebook group that posts a feed of health messages in which 25% are focused on preventing indoor tanning and 75% are focused on other health topics (eg, nutrition, physical activity, etc). Indoor tanning increases in December, peaking in March for seasonal tanners (eg, event and regular seasonal tanners) [37,38]. During these months, indoor tanning posts will be scheduled at a higher frequency (30% of posts).

### Control Condition

In the control condition, participants will enter a private Facebook group that posts a feed of health messages in which 25% are focused on preventing prescription drug abuse and 75% are focused on the same health topics as the intervention condition. We selected prescription drug abuse as our “control” content, because (1) it is completely unrelated to tanning, thus not likely to impact our primary outcomes, and (2) it is an emerging issue of great interest and relevance to young adults in east Tennessee. This 25% segment of posts is the only difference between the intervention and control conditions.

### Setting

The study is being conducted in east Tennessee given that Tennessee has a parental permission law for indoor tanning and a high prevalence of indoor tanning, with 31% of adolescent girls reporting indoor tanning in a recent study [39]). Tennessee’s indoor tanning policy (Tennessee Code Ann. § 68-117-104) requires that children under the age of 14 be accompanied by a parent if they use a commercial tanning facility and those ages 14 to 17 must have parents visit the tanning facility to sign a permission form in-person. The form only needs to be signed once at each facility. Communities in the region are diverse in size and rural/urban context and 84% of the public school population is white, the racial group most likely to indoor tan and at highest risk for melanoma [40].

### Participants

A cohort of 2000 mother-teen daughter dyads will be recruited to participate in this study. Only mothers and daughters will be recruited because female teens are nearly 4 times more likely to indoor tan (23% in 2009-2011 Youth Risk Behavior Survey) than male teens (6% [41]) and evidence suggests maternal permissiveness is a predictor of indoor tanning. The literature on indoor tanning by male teens is nascent with minimal data on predictors or effective intervention strategies.

Eligible mothers will meet the following criteria: (1) live in Tennessee, (2) have a daughter aged 14 to 17, (3) consent to participate, (4) read English, (5) complete the baseline survey, and (6) have a Facebook account (or be willing to create one). History of indoor tanning is not required for inclusion. Because public policy requires broad public support not just support by those most affected, ethnic minority mothers who are interested in participating (mainly African Americans; 14% are minority, 86% are non-Hispanic white) will be enrolled. The planned sample size was increased to ensure that statistical power is based on the number of non-Hispanic, white mothers. This approach will also allow for an evaluation of how the intervention affects ethnic minority mothers’ support for indoor tanning bans.

Eligibility criteria for teen daughters include having a mother enrolled in the study and assenting to participate. Daughters will be enrolled regardless of their indoor tanning behavior and the sample will be inflated to insure adequate numbers of non-Hispanic whites. Daughters will be enrolled only to complete assessments. They will not have access to the Facebook group. If a mother has more than one eligible daughter, she will provide information for the one with the nearest birthday, as instructed on the enrollment website.

### Sample Size and Power Calculations

Using public high school enrollment data, we estimate that approximately 20,000 eligible mothers and 25,000 eligible daughters reside in the east Tennessee region. Effect sizes for similar previous studies are in the range of moderate to large for our primary and secondary outcomes (mothers’ permissiveness and indoor tanning behavior, respectively). For example, Baker et al [42] found that mothers’ permissiveness and daughters’ perceptions of indoor tanning declined following a 1-month intervention at an immediate posttest (mother: baseline mean 2.59 [SD 1.03], follow-up mean 2.47 [SD 0.86]; daughter: baseline mean 3.12 [SD 1.32], follow-up mean 2.74 [SD 1.1]) compared with controls (mother: baseline mean 3.02 [SD 1.08], follow-up mean 2.98 [SD 1.10]; daughter: baseline mean 3.12 [SD 1.24], follow-up mean 3.40 [SD 1.04]). Likewise, for indoor tanning behavior, Hillhouse et al [43] found the number of sessions in the past 3 months among indoor tanners was reduced in an intervention condition at 6 months (baseline mean 4.67 [SD 0.60], follow-up mean 6.80 [SD 0.93]) compared with controls (baseline mean 4.48 [SD 0.55], follow-up mean 10.90 [SD 0.93]). The frequency of indoor tanning observed in the proposed study will likely be lower, because not all mothers and daughters will indoor tan (31% of adolescent girls indoor tanned in a recent study in east Tennessee; indoor tanning is higher in rural areas [44]). Still, the effect size between conditions is expected to remain moderate to large.

We used the Optimal Design software package (version 3.0) [45] to determine sample size. Assuming a 2-tailed alpha of 0.05, a moderate effect size of d=0.50, and an intraclass correlation of 0.05 within each Facebook private group, we far exceed a power of 0.80 with 50 Facebook private groups each consisting of 25 mothers (total n=1250 mothers and 1250 daughters). We increased this sample size to account for the proportion of minority mothers and daughters (15%) we expect to recruit to achieve the needed sample size of non-Hispanic whites, the racial/ethnic group most likely to indoor tan and with the highest rates of melanoma [40]. We further inflated the sample to account for an expected loss to follow-up of 30% by 12 months (20% at 6 months). Thus, we will recruit initial samples of 2100 mothers and 2100 daughters (42/Facebook group) at baseline and expect to successfully assess 1680 in each sample (approximately 34/Facebook group) at the 6-month follow-up and 1470 in each sample (approximately 29/Facebook group) at the 12-month follow-up, with the final samples containing 1250 non-Hispanic white mothers and 1250 non-Hispanic white daughters for analysis.

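### For mothers' permissiveness, the cited trial's own figures show a net effect of d about 0.08, not the moderate-to-large effect claimed in support of d=0.50

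*Protocol article*

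**What the plan says.** All of this is in the protocol article, Sample Size and Power Calculations, unless stated otherwise.

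- The section opens its justification with "Effect sizes for similar previous studies are in the range of moderate to large for our primary and secondary outcomes" and identifies these outcomes as mothers' permissiveness and tanning behavior, respectively.
- Its example for permissiveness is a trial of a 1-month intervention with an immediate posttest. The intervention arm is "mother: baseline mean 2.59 [SD 1.03], follow-up mean 2.47 [SD 0.86"; the control arm is "mother: baseline mean 3.02 [SD 1.08], follow-up mean 2.98 [SD 1.10". Daughters went from 3.12 to 2.74 on intervention and from 3.12 to 3.40 on control.
- For tanning sessions it cites a second trial with follow-up means of 6.80 and 10.90, each with a printed SD of 0.93.
- It concludes: "Still, the effect size between conditions is expected to remain moderate to large".
- The calculation then runs: "Assuming a 2-tailed alpha of 0.05, a moderate effect size of d=0.50, and an intraclass correlation of 0.05 within each Facebook private group", with 50 groups of 25 mothers (1250 in all), and reports power well above 0.80.

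Mothers' permissiveness is among the primary outcomes in the Abstract, the Hypotheses and the Measures section.

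**The concern.** The two arms of mothers in the cited trial started 0.43 points apart. A follow-up comparison that ignores this gives about 0.5 SD, close to the planning value. The comparison that bears on an intervention effect takes the starting difference into account, and it is far smaller. The text does not mention the imbalance and presents the result as a decline relative to controls.

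At stake is how the stated power is read. The assurance applies to an effect that the cited mothers' figures do not show. If mothers' permissiveness came out null, a reader relying on that assurance could rule out more than the design allows.

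**Working it through.** **Inputs.** Means and SDs as quoted in the sample size section; 50 groups of 25, intraclass correlation 0.05, two-sided alpha 0.05 (same section); 25 groups per condition (Study Design).

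**1. The plan's own power figure.** In SD units, the standard error of the difference is sqrt(4 × (0.05 + 0.95/25)/50) = sqrt(4 × 0.088/50) = 0.0839. Equivalently, the design effect is 1 + 24 × 0.05 = 2.20 and the effective size is 625/2.20 = 284 per arm. At d=0.50 the noncentrality is 0.50/0.0839 = 5.96. Power from a noncentral t on 48 df is above 0.999, so the stated power reproduces.

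**2. Mothers in the cited trial.**
- Change, intervention: 2.47 - 2.59 = -0.12. Change, control: 2.98 - 3.02 = -0.04. Net: -0.08.
- Pooled SD at baseline: sqrt((1.03² + 1.08²)/2) = 1.055. At follow-up: sqrt((0.86² + 1.10²)/2) = 0.987.
- Net d: 0.08/1.055 = 0.076 to 0.08/0.987 = 0.081.
- Follow-up gap: 2.98 - 2.47 = 0.51, and 0.51/0.987 = 0.52.
- Baseline gap: 3.02 - 2.59 = 0.43, and 0.43/1.055 = 0.41.
- Share of the follow-up gap present at baseline: 0.43/0.51 = 84%.

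**3. Daughters in the cited trial.** Baselines are equal at 3.12. Net change: (2.74 - 3.12) - (3.40 - 3.12) = -0.66. Pooled SDs are 1.281 (baseline) and 1.070 (follow-up), so d = 0.52 to 0.62. These figures support 0.50.

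**4. Baseline adjustment for mothers.** The adjusted difference is 0.51 - b × 0.43, where b is the pre-post slope. The article does not give b, so the values below are assumptions. d uses the follow-up SD of 0.987, and power uses the unadjusted standard error of 0.0839.

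| Slope b | Adjusted difference | d | Power |
|---|---|---|---|
| 1.0 (change score) | 0.080 | 0.08 | about 15% |
| 0.9 | 0.123 | 0.12 | about 31% |
| 0.8 | 0.166 | 0.17 | about 50% |
| 0.6 | 0.252 | 0.26 | about 85% |
| 0.5 | 0.295 | 0.30 | about 94% |

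**5. Minimum detectable effect at 80% power.** (2.011 + 0.849) × 0.0839 = 0.24.

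**6. Session counts as printed.** (10.90 - 6.80)/0.93 = 4.4 SDs.

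**The case against.** **The planning value is only an assumption, and the power is right for it.** This stands. The article never says that d=0.50 was calculated from this trial. The link is inferred from the order of the text and from the 0.52 at follow-up. There is no error in the power arithmetic; the fault lies in the support offered for the effect size.

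**The cited data do contain an effect of about 0.5.** True for daughters' perceptions, also a primary outcome in the Abstract and Hypotheses. A reader might infer that no cited result supports 0.50; the daughters' figures rule that out.

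**The 15% is the low end.** Also true. It rests on a change-score point estimate, quoted without a sample size or interval, from a 1-month intervention, whereas this trial intervenes for 12 months. If this trial's own analysis also adjusted for baseline, with individual-level residual variance reduced by 1 - r² (r = b × 1.055/0.987) and group-level variance unchanged, power at slopes 0.8, 0.6 and 0.5 would be about 66%, 91% and 96%. The Analysis Plan does not state such an adjustment. A reader might infer that the trial is underpowered; the documents do not show that for every plausible effect.

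**Mothers' permissiveness is not ranked first, and the cited trial is introduced only as an example.** Both correct. The Measures section lists the primary outcomes without an order, and the Introduction cites other work on maternal permissiveness, though with no figures.

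**Tanning behavior.** A reader might go on to infer that the printed session SDs are really standard errors, or that a large share of non-tanners leaves tanning underpowered. The first needs the cited source. The second needs an assumed effect among tanners and an assumed spread of counts. Neither can carry this point.

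**Conclusion.** The point holds for mothers' permissiveness. The claim of moderate-to-large prior effects on that outcome is contradicted by the figures in the same paragraph: net d is about 0.08, and about 0.12 to 0.30 under assumed baseline slopes of 0.9 to 0.5. All are below the 0.50 used for planning. Recognising this takes only the article's own means and SDs.

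The power consequences rest on the article's 50 groups of 25 and intraclass correlation of 0.05. The design has 80% power at d of about 0.24, which is three times the net change-score effect but inside the baseline-adjusted range. The conclusion is therefore that d=0.50 lacks support for this outcome and that the assurance drawn from it is too strong. It is not that the sample size is wrong.

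A secondary matter for the sponsor to check: the printed session-count SDs of 0.55 to 0.93 imply an effect of about 4.4 SDs, which is hard to credit for tanning counts.

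**What to change.** Keep the sample size. In Sample Size and Power Calculations:

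1. Limit the moderate-to-large description drawn from the cited permissiveness trial to daughters' perceptions.
2. State the mothers' result in that trial as a net 0.08 points, d about 0.08, rising to about 0.30 depending on the baseline adjustment assumed, and mention the 0.43-point baseline difference.
3. For mothers' permissiveness, replace the statement that power is well above 0.80 with the minimum detectable effect: d of about 0.24 at 80% power with 50 groups of 25 and intraclass correlation 0.05.
4. Verify the session-count SDs against their source before using them as effect-size support.

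The cost is rewording and one check of a source. No participants are added and the analysis does not change. The drawback is that the stated power for mothers' permissiveness becomes less favorable.

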### Analysis Plan

Hypotheses will be tested using a multilevel (mother-daughter dyad nested in Facebook private group) structural equation model (SEM). The following specific tests within the multilevel SEM will be used to evaluate the primary hypotheses in order to examine the effects of the social media campaign on indoor tanning outcomes. For the hypothesis regarding mothers’ permissiveness for daughters to indoor tan, mothers’ permissiveness (a level 1 variable) will be specified as a multiple indicator latent construct and regressed on the treatment indicator (campaign with prescription drug messages (control) vs campaign with indoor tanning messages (intervention), a level 2 variable). Similarly, for the hypothesis regarding daughters’ perceptions of mothers’ permissiveness, daughters’ perceptions (a level 1 variable), a multiple indicator latent construct, will be regressed on the treatment indicator (a level 2 variable). Mother and daughter perceptions will be correlated. In testing the hypothesis relating to indoor tanning frequency, mothers’ and daughters’ tanning (level 1 variables) will be specified as a count of the number of tanning sessions (in the past 3 months) and regressed on the treatment indicators (a level 2 variable), using a zero-inflated negative binomial distribution (which simultaneously models the effect of the intervention on the prevalence and frequency (among tanners) of tanning sessions). Mother and daughter behavior will be correlated. Finally, the hypothesis relating to mothers’ support for IT bans will be tested by regressing mothers’ signatures on the Web-based petitions (a level 1 binary variable—signed or not signed) on the treatment indicator (a level 2 variable) in a multilevel SEM.

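### The stated power covers a continuous outcome such as permissiveness; it is not supported for indoor tanning, and the claim that the tanning effect stays moderate to large with non-tanners included conflicts with the protocol's own figures

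*Protocol article*

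**What the plan says.** **Power.** Sample Size and Power Calculations contains one calculation: "We used the Optimal Design software package (version 3.0) [45] to determine sample size". Its inputs are: "Assuming a 2-tailed alpha of 0.05, a moderate effect size of d=0.50, and an intraclass correlation of 0.05 within each Facebook private group". Its conclusion is that "we far exceed a power of 0.80 with 50 Facebook private groups each consisting of 25 mothers (total n=1250 mothers and 1250 daughters").

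**Tanning effect.** The same section supports the tanning effect with a study of indoor tanners: 6.80 sessions in three months at follow-up under intervention and 10.90 under control, each with a printed SD of 0.93. It accepts that not all mothers and daughters will tan, gives 31% for adolescent girls in east Tennessee, and then states: "Still, the effect size between conditions is expected to remain moderate to large".

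**Planned test.** The Analysis Plan tests mothers' and daughters' tanning as three-month session counts, "using a zero-inflated negative binomial distribution (which simultaneously models the effect of the intervention on the prevalence and frequency (among tanners) of tanning sessions").

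**Maternal prevalence.** The only figure is in the Introduction, as background: "8% to 14% of caregivers [17,21-24] (mainly mothers) reported indoor tanning in the past year". Participants states that mothers need no history of tanning to be enrolled.

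**Status of the outcome.** The Abstract, Hypotheses and Measures treat tanning as primary. The power section calls permissiveness primary and tanning secondary.

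**The concern.** A standardized difference of 0.50 with an ICC describes a mean compared across everyone. A zero-inflated count carries its information differently: the prevalence part depends on how many people tan, and the frequency part depends almost wholly on the tanners. An effect seen among tanners also shrinks when it is averaged over a sample in which most people have zero sessions. The protocol recognises the dilution but asserts, without a calculation, that the effect size survives it.

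The practical risk is in reading the results. A null finding on mothers' tanning, from a trial described as having power far above 0.80, would be taken as evidence of no effect when the design may simply have had too few maternal tanners to show one.

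**Working it through.** **1. The plan's own figure.** Inputs: 50 groups of 25 (25 groups per arm), d=0.50, ICC 0.05, two-sided alpha 0.05.
- SE(d) = √[4 × (0.05 + 0.95/25)/50] = √(4 × 0.088/50) = 0.084, with 48 df.
- Power at d=0.50 is 0.9999. The smallest d with 80% power is about 0.24.
- The inflation also reproduces: 1250/0.85/0.70 = 2101, against 2100 planned.

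So the statement is right for a continuous outcome. That the outcome was taken as continuous is inferred from the use of d with an ICC; the protocol does not say so.

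**2. Dilution of the cited tanning effect.** Let a share p of each arm tan (the same in both arms), with mean m sessions and variance v among tanners. Then

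d = p(10.90 − 6.80) / √{average over arms of [p·v + p(1−p)·m²]}.

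With the printed SD, v = 0.93² = 0.865. For daughters at p=0.31:
- numerator 0.31 × 4.10 = 1.271
- arm variances 25.68 and 10.16, average 17.92, square root 4.23
- d = 1.271/4.23 = 0.30

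An SD of 0.93 is favourable to the plan: Poisson counts with these means would have SDs of √6.80 = 2.6 and √10.90 = 3.3. The table therefore adds v = m + αm², with α from 0.5 to 2. The protocol gives no dispersion, so this range is an assumption. Power uses the SE from step 1.

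| Group | p | d, printed SD | Power | d, α 0.5 to 2 | Power |
|---|---|---|---|---|---|
| Daughters | 31% | 0.30 | 0.94 | 0.22 to 0.15 | 0.73 to 0.42 |
| Mothers | 14% | 0.18 | 0.56 | 0.14 to 0.10 | 0.37 to 0.21 |
| Mothers | 8% | 0.13 | 0.34 | 0.10 to 0.07 | 0.23 to 0.14 |

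None of these reaches the 0.50 that the protocol itself calls moderate.

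**3. Prevalence part of the planned model, mothers.** Inputs:
- The odds ratio equivalent to d=0.50 is exp(−0.50 × π/√3) = 0.404.
- The design effect is 1 + 24 × 0.05 = 2.2, so the effective size is 625/2.2 = 284 per arm.
- Power comes from a two-proportion z test.

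Results:
- 8% falling to 3.4%: 0.66
- 10% to 4.3%: 0.75
- 12% to 5.2%: 0.82
- 14% to 6.2%: 0.88
- 31% to 15.4%: 0.99

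If the ICC of 0.05 is read on the latent scale, simulated power is 0.88 at 8% and 0.97 at 14%.

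**4. Frequency part, mothers.** At 8% to 14% there are about 100 to 175 tanners among 1250 mothers.
- For d=0.50 among tanners, power is 0.68 to 0.88.
- For the cited ratio 6.80/10.90 = 0.62, a clustered two-part simulation (assumed gamma shape 1, group-level t tests, 1500 runs) gives 0.57 at 8% and 0.81 at 14%. At 31% it gives 0.99.

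The full multilevel model was not fitted in that simulation.

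**5. Recall window.** Primary Outcomes asks about the past year; the Analysis Plan counts three months. A shorter window lowers the non-zero share. At an assumed 4%, the step 3 calculation gives power 0.39 (0.62 with the ICC on the latent scale).

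**The case against.** The strongest reply is that 8% to 14% is not this trial's rate. It is a general figure for caregivers, and east Tennessee was chosen because tanning is common there. Among teens the contrast is 10% to 15% in the background against 31% locally. If mothers differ similarly, the prevalence part passes 0.80 at about 12% and reaches 0.99 at 31%. This stands. It means that power for mothers' tanning is unknown, not that it is low.

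Second, the low figures in step 2 compare raw means, which is not the planned test. That also stands. Those figures bear on the sentence about effect size. Power for the planned analysis has to be read from steps 3 and 4, where results fall on both sides of 0.80 for mothers and are high at 31%.

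Third, the power section labels tanning secondary, and sizing a trial on its lead outcome is conventional. That would be an answer if the label were consistent, but three other places call tanning primary.

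A reader might also infer that a whole-sample d of 0.50 is impossible for mothers. The figures do not go that far. If the intervention ended all tanning at 8% to 14% prevalence, with almost no spread among tanners, d would be 0.29 to 0.40 in control-SD units but 0.42 to 0.57 with a pooled SD. That makes 0.50 implausible on this scale at those rates, and the ceiling rises with prevalence.

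**Conclusion.** The point holds as a matter of scope. The power statement is correct for permissiveness and is not supported for tanning. The sentence on effect size is not borne out: with the protocol's own session means, and even with the printed SD, the whole-sample effect is at most d=0.30 for daughters and about 0.13 to 0.18 for mothers at the background rate. This assumes equal prevalence in the two arms; a simultaneous fall in prevalence would raise d.

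It would be wrong to conclude that the trial is underpowered for mothers' tanning, or that the power claim is an arithmetic error. For an effect equivalent to d=0.50, power in either part of the planned model runs from about 0.66 to 0.88 at 8% to 14% prevalence and is about 0.99 at 31%. The protocol states neither an expected maternal rate nor a dispersion, and its two recall windows conflict.

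**What to change.** - In Sample Size and Power Calculations, limit the claim of power far above 0.80 to the permissiveness outcomes.
- In the same section, remove or correct the sentence that the effect stays moderate to large once non-tanners are included.
- Give tanning power separately for the prevalence and frequency parts, and for mothers and daughters, over a stated range of prevalence and dispersion and for the recall window that will be analysed.
- Reconcile the status of tanning between the Abstract, Hypotheses and Measures (primary) and the power section (secondary), and the window between Primary Outcomes and the Analysis Plan.
- State that a null result on mothers' tanning will be reported with its confidence interval and not as evidence of no effect.

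The authors need not declare power below 0.80, since that would rest on an assumed prevalence and dispersion. The cost is some rewording and a short simulation, with no extra participants. The price is a less favourable stated power for tanning.
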